**Fig. 2 Fig2:**
[figure not shown]
Study procedures to investigate clinical and biomechanical outcome after dynamic and static MPFL reconstruction

### Dynamic and static MPFL reconstruction technique

We will compare the established static MPFL reconstruction technique according to Schöttle et al. [20] with the dynamic reconstruction technique according to Becher et al. [29]. Both techniques use the gracilis tendon for patella stabilization. The static Schöttle-technique harvests the autologous gracilis tendon and inserts the armed tendon at the medial femur condyle (slightly anterior to an elongation of the posterior femoral cortex in between the proximal origin of the medial condyle and the most posterior point of Blumensaat’s line) and at two insertion points at the medial margin of the patella (superomedial corner of the patella and the midpoint of the medial margin of the patella). A fixation is performed with three suture anchors. In the dynamic Becher-technique the distal gracilis tendon is detached periosteal at its anatomical insertion. The freed tendon end is armed and redirected between the quadriceps fascia and the joint capsule to the patella, using the sartorius fascia as a hypomochlion. The fixation of the tendon at the mid third of the medial margin of the patella is performed with a suture anchor according to Bartsch et al. [45].

### Measurements

All study related data will be entered into and stored using the REDCap web-based electronic data capture system [46]. The digital collection system Heartbeat will be used to administer the patient reported outcome questionnaires and data will be transferred to REDCap.

#### Clinical assessment

*Clinical outcome* Assessments will be performed in a preoperative screening, at the hospitalization time and at five postoperative follow-ups. Patient reported knee function, anterior knee pain and quality of life will be recorded by the Kujala-score [35], Banff-II-score [36], IKDC-2000 [36] and the EQ-5D-5L [37]. Moreover, pain level using the numeric rating scale, operation and hospitalization time and general satisfaction with treatment outcome will be assessed.

*Surgical outcome* Surgical outcome will be assessed as: (1) recurrent patella dislocations: the number and time of dislocations will be recorded based on patient recall; (2) revision surgery: number, type and time interval from the MPFL surgery to revision surgery will be recorded based on our operation schedule or patients recall; and (3) other occurring complications (e.g., infection, wound healing disorder): number, type and time interval from MPFL surgery to occurring complication will be recorded based on patients recall and clinicians examination.

#### Biomechanical assessment

Biomechanical outcome will be assessed preoperatively and 1 year postoperatively by assessing isokinetic muscle strength, gait asymmetry, single-legged drop landing, and timing of muscle activity. First, participants will warm up by walking for 5 min at self-selected speed on a treadmill.

Muscle strength will be measured bilaterally using a dynamometer (Biodex System 4 Pro: Biodex Medical Systems, Shirley, NY, USA). For the knee, maximum isokinetic flexion and extension torques will be collected between full extension and 90° flexion at a movement speed of 60°/s (5 repetitions) and 240°/s (15 repetitions) [47]. Maximum joint torques in each movement direction will be recorded for each joint and normalized to body weight. During these tests, electromyographic (EMG) data will be collected using a 16 channel EMG system (myon AG, Schwarzenberg, Switzerland, sampling rate 2400 Hz). Surface electrodes will be placed bilaterally on the vastus medialis and lateralis, semitendinosus, biceps femoris, gracilis, gluteus medius, tibialis anterior, and gastrocnemius medialis muscles following the guidelines of the SENIAM project (Surface Electromyography for the Non-Invasive Assessment of Muscles) [48] and Lovell et al. [49].

Participants will then perform an instrumented gait analysis on an overground walkway with two embedded force plates (Kistler force plate 9260AA6, Kistler AG, Winterthur, Switzerland; sampling rate 2400 Hz) and on a treadmill with an embedded plantar pressure plate (h/p/cosmos, Zebris FDM-T, Isny, Germany; 7168 sensors; area, 1.5 * 0.5 m; range, 1–120 N/cm^2^; precision, 1–120 N/cm2 ± 5%; sampling rate, 120 Hz). Simultaneously with the plantar pressure or force data, kinematic and electromyographic (EMG) data will be collected using a 10 camera Vicon system (Vicon, Oxford, UK; frame rate 240 Hz) and the 16 channel EMG system (see above). To assess 3D joint angles, reflective markers will be placed on predefined anatomical landmarks on the pelvis and lower legs [50]. Subjects will complete overground walking trials on the walkway with embedded force plates. Participants will then walk for 2 min on the treadmill at 0% slope at their preferred walking speed and at 1.2 m/s. Additionally, uphill and downhill treadmill walking (positive and negative slope of 10%) will be measured at 85% of the preferred walking speed. For all conditions, kinematic, EMG and pressure data will be recorded. Subsequently, the treadmill speed will be increased to preferred running speed, and data for 2 min running will be recorded.

To assess muscle activity and leg axis stability, a single-leg vertical drop landing will be performed. As a pretest and to get accustomed with the task, patients will first perform a bipedal drop landing. Participants will then be given a verbal description of the single-leg landing task prior to testing. Standing erect upon only the tested leg with the foot in neutral position, participants will step off a 20 cm high platform. Participants will be instructed to land in the center of the force-plate on the tested leg only. To control for countermovement, participants will be restricted to perform the drop landing with hands upon hips and the contra-lateral knee joint flexed to 90°. All more demanding functional task (running, drop landing) will be performed if patients feel comfortable and do not experience pain during these tasks.

Maxima and minima will be calculated for continuous kinematic and kinetic data [51]. EMG data will be filtered with a modified band pass of 15 Hz to 450Hz [52]. For each muscle, the root mean square of the EMG signal for the stance phase of walking and running will be calculated and normalized to the maximum signal intensity obtained during maximum voluntary contraction [53]. Timing of the gracilis muscle will be assessed as on- and offset relative to the gait cycle. According to Stokes et al. [54], gracilis onset will be determined as the time when the processed EMG signal exceeded a threshold of three standard deviations above a baseline mean and as offset, when the processed EMG signal falls below a threshold of three standard deviations above a baseline mean. For all muscle strength, gait spatio-temporal, and muscle activity parameters, the asymmetry index (AI) will be calculated according to Hodt-Billington et al. [55] as$$AI= \left|1- \frac{Limb_{lower\_value}}{Limb_{higher\_value}}\right|$$

For all kinematic and kinetic parameters (measured in degrees respective Nm/kg), the asymmetry index will be defined as$$AI= \left|\mathrm{Limb_{higher\_value}}-\mathrm{Limb_{lower\_value}}\right|$$

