## Background

High joint reaction forces in the patellofemoral joint of up to several times body weight [1, 2] are reflected in patellar cartilage being the thickest in the body with a patellar cartilage thickness of up to 7.5mm [3]. Articular cartilage damage is common, with 44.6% cartilage lesions of the patellofemoral joint reported in knee arthroscopies [4]. The pathogenesis of these lesions may result from acute trauma or altered joint loading due to patella instability. After patella dislocation, the incidence of acute osteochondral or chondral injuries is up to 95% after initial patella dislocation [5]. Moreover, chronic cartilage damage has been described at 13-year follow up with patellofemoral osteoarthritis in 22% in patellar instability knees compared to 11% in contralateral healthy knees [6].

Misshaped structures such as a high riding patella (patella alta) [7] or trochlear dysplasia [8] are risk factors for patella instability. The medial patellofemoral ligament (MPFL) has been shown to be the main dynamic stabilizer of the patella against lateral translation [9], especially when the patella has not yet engaged in the trochlear groove (knee flexion < 30°) [10]. After initial patellar dislocation, the MPFL is injured in 94% of the cases [11]. Because the redislocation rate of the patella after conservative management reaches up to 67% [12, 13] most authors recommend surgical management of these cases, and a variety of surgical procedures has been developed [14].

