Patients with dynamic MPFL reconstruction will have less asymmetry in muscle strength and lower extremity gait kinematics and kinetics than patients with static MPFL reconstruction. To date, comparable biomechanical data of the dynamic MPFL reconstruction technique do not exist.

#### Specific Aim 3

Determine whether the reported success for patella stabilization in dynamic MPFL reconstruction is due to muscle contraction or to the passive tenodesis effect.

#### Hypothesis 3

The function of the gracilis muscle will change from a knee flexor with normal activity from pre-swing throughout the entire swing phase to the beginning of the loading response after the surgery to an isolated patella stabilizer, specifically depending on the knee flexion angle. We anticipate that muscle activity will shift more toward the loading response and the whole stance phase at knee angles < 30° of flexion. The capability and efficacy of such muscle transfer procedures have been described for other procedures such as rectus femoris transfer in children with cerebral palsy [39, 40]. The gracilis muscle reaches forces up to 300 N from 0–60° knee flexion [41] indicating that the gracilis muscle is adequate for patella stabilization.

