#### Inclusion criteria

Inclusion criteria are: isolated MPFL reconstruction due to patella instability in patients with closed growth plates; patella dislocation; Patella-Instability-Severity (PIS) score [42] ≤ 3 with concomitant flake fracture; PIS score ≤ 4 with clinical asymptomatic trochlea dysplasia (patella stability between 30 and 60° knee flexion); and no other clinically relevant static risk factors as patella alta or increased tibial tuberosity trochlear groove distance.

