#### Exclusion criteria

Exclusion criteria are: combined procedures with trochleoplasty (trochlea dysplasia Type C or D according to Dejour et al. [43] with clinical instability between 30 and 60° of knee flexion); combined procedures with cartilage transplantation; high grade patellofemoral arthritis (Kellgren Lawrence [44] score ≥ 3); combined procedures with femoral or tibial osteotomy; clinically eminent valgus axis (> 15° valgus); femoral internal rotation > 20°; tibial external rotation > 40°; instability of the cruciate or collateral ligaments; known significant musculoskeletal disease or cognitive impairment; and patient age < 14 years.

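### Hypothesis 2 uses the opposite leg as its only reference without securing that this leg is sound, so less asymmetry need not mean better recovery of the operated leg

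*Protocol article*

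**What the plan says.** All references are to the Protocol article.

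- **Hypothesis 2, under Specific aims:** "Patients with dynamic MPFL reconstruction will have less asymmetry in muscle strength and lower extremity gait kinematics and kinetics than patients with static MPFL reconstruction". The hypothesis is worded on asymmetry alone.
- **Biomechanical assessment, ratio index:** "For all muscle strength, gait spatio-temporal, and muscle activity parameters, the asymmetry index (AI) will be calculated" as the absolute value of one minus the lower limb value over the higher.
- **Biomechanical assessment, difference index:** "For all kinematic and kinetic parameters (measured in degrees respective Nm/kg), the asymmetry index will be defined as" the absolute difference between the higher and the lower limb value. Neither formula identifies the operated limb.
- **Biomechanical assessment, data:** "Muscle strength will be measured bilaterally using a dynamometer", with torque normalized to body weight. Measurements are taken before surgery and at 1 year.
- **Inclusion criteria:** "isolated MPFL reconstruction due to patella instability in patients with closed growth plates; patella dislocation". The list sets no condition on the opposite knee.
- **Exclusion criteria:** the nearest items are "instability of the cruciate or collateral ligaments; known significant musculoskeletal disease or cognitive impairment; and patient age < 14 years". No side is named for ligament instability, and the musculoskeletal item is not defined.
- **Participants and Statistical analysis:** randomization is in blocks within center. Groups are compared by differences in means with confidence intervals and p-values. The relation to baseline values will be examined, but the opposite knee is not mentioned.

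**The concern.** An index of one leg against the other describes recovery of the operated leg only if the other leg is sound. Here there is reason to doubt that in some patients. The Background says that "Misshaped structures such as a high riding patella (patella alta) [7] or trochlear dysplasia [8] are risk factors for patella instability", and these are features of anatomy that need not be confined to one side. The inclusion criteria bar clinically relevant patella alta but admit clinically asymptomatic trochlear dysplasia. A site could hardly read patellar instability, the trial's own indication, as an excluding musculoskeletal disease. A patient whose other knee is unstable or has been operated on therefore appears eligible, and surgery on that knee before the 1-year visit would also move the index.

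At stake is what Hypothesis 2 can conclude. A lower mean index in the dynamic arm would be read as better recovery, although for these patients it may reflect the state of the other leg.

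**Working it through.** The point rests on no figure stated in the plan. The only related figure is the number of patients, which was set for the Kujala score: 54 / (1 - 0.10) = 60, or 30 per arm with 27 expected to be evaluable. All limb values below are assumptions.

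**Step 1: what the index does in single patients.** Ratio index AI = |1 - lower/higher|, with assumed torques in Nm/kg:

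| Operated | Opposite | AI |
|---|---|---|
| 2.5 | 2.5 | 0.00 |
| 1.5 | 2.5 | 1 - 1.5/2.5 = 0.40 |
| 1.5 | 1.5 | 0.00 |
| 1.5 | 1.6 | 1 - 1.5/1.6 = 0.06 |
| 2.0 | 1.5 | 1 - 1.5/2.0 = 0.25 |

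Two equally weak legs score like two sound ones. A better operated leg beside a weak one scores worse than two weak legs. The difference index behaves in the same way: |2.0 - 1.5| = 0.5 against |1.5 - 1.5| = 0.

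**Step 2: the contrast between arms.** Assume operated legs at 0.80 (static) and 0.90 (dynamic) of normal, and an opposite leg at c. The unsigned contrast is static AI minus dynamic AI. The signed index is 1 - operated/opposite, and its contrast is (0.90 - 0.80)/c.

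| c | Static AI | Dynamic AI | Unsigned contrast | Signed contrast |
|---|---|---|---|---|
| 1.00 | 0.200 | 0.100 | 0.100 | 0.100 |
| 0.95 | 0.158 | 0.053 | 0.105 | 0.105 |
| 0.90 | 0.111 | 0.000 | 0.111 | 0.111 |
| 0.85 | 0.059 | 0.056 | 0.003 | 0.118 |
| 0.80 | 0.000 | 0.111 | -0.111 | 0.125 |
| 0.70 | 0.125 | 0.222 | -0.097 | 0.143 |

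Mild impairment of the opposite leg does not dilute the contrast. Once the opposite leg is weaker than the dynamic arm's operated leg, the unsigned contrast shrinks and then reverses. The signed contrast does not shrink.

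**Step 3: mixtures.** With a share p of affected patients, the expected contrast is (1 - p) × 0.100 + p × (contrast at c).

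| c | p = 20% | p = 40% |
|---|---|---|
| 0.95 | 0.101 | 0.102 |
| 0.90 | 0.102 | 0.104 |
| 0.85 | 0.081 | 0.061 |
| 0.80 | 0.058 | 0.016 |
| 0.70 | 0.061 | 0.021 |

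**Step 4: adding variability.** A simulation used the same operated-leg values, c = 0.80, an SD of 0.08 per limb and limbs drawn independently. Power is for a two-sided t-test with 27 per group.

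| Share affected | Mean AI, dynamic vs static | Difference | Power |
|---|---|---|---|
| 0% | 0.119 vs 0.199 | 0.080 | 90% |
| 20% | 0.121 vs 0.180 | 0.058 | 64% |
| 40% | 0.124 vs 0.161 | 0.037 | 30% |
| 100% | 0.132 vs 0.104 | -0.028 | order reversed |

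**Step 5: chance imbalance.** With 27 per arm and a share of 20% to 30%, a gap of 4 or more affected patients has probability 23% to 30%. At c = 0.85, 4 extra affected patients out of 30 shift the static mean by 4/30 × (0.200 - 0.059) = 0.019 and the dynamic mean by 4/30 × (0.100 - 0.056) = 0.006.

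**The case against.** The case on the other side is substantial.

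- **The loss comes largely from the unsigned index.** This stands. In Step 2 the fall to 0.003 occurs at one opposite-leg value, midway between the two operated-leg values, where taking absolute values almost cancels the contrast. A signed index gives 0.118 there. A sign does not cure everything, however: two equally impaired legs still score zero.
- **A reader might infer that such patients always pull the index towards zero.** They do not. The 2.0/1.5 pair scores 0.25, and 0.90 beside 0.70 scores 0.222 against 0.100 with a sound opposite leg. The index can move either way.
- **A reader might infer that a few such patients, unevenly allocated, could create or hide the whole effect.** Step 5 does not support that: the shift is about 0.02 against an assumed contrast of 0.10. Randomization also balances opposite-knee status in expectation, so this is not systematic bias between arms.
- **Operated-limb data exist.** True: torque normalized to body weight, kinematic and kinetic extremes, and gracilis timing are obtained. Hypothesis 2 is nevertheless worded on asymmetry alone.
- **The baseline comparison might deal with it.** Not by itself, because a preoperative asymmetry index has the same reference limb.
- **The full protocol or SAP may cover it.** Case-report items and subgroup rules may well be there, and their absence from an article is no fault. The article itself, however, fixes the eligibility list, both formulas and the wording of the hypothesis, and the difficulty lies in how these combine.

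**Conclusion.** The point holds in a limited form. In patients with an impaired opposite knee the index does not measure recovery of the operated leg, and the stated criteria do not clearly keep such patients out. This follows from the formulas and needs no assumption about frequency.

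The effect on the trial's result cannot be fixed from the document, which gives neither the share of such patients nor their degree of impairment. Under the assumptions shown, a contrast of 0.10 becomes 0.058 to 0.102 at a 20% share and 0.016 to 0.104 at 40%. The low ends apply only when the opposite leg is about as weak as the operated leg, or weaker, and the index is unsigned.

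The consequence is a diluted or misread contrast in a non-primary hypothesis. The Kujala comparison and its sample size are untouched. Nor does the document support abandoning asymmetry as an outcome: it is a reasonable measure where the opposite leg is sound, and replacing it altogether would be a trade-off rather than a correction.

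**What to change.** 1. Record dislocation and surgery of the opposite knee at baseline, and new surgery on it by the 1-year visit. Table 1 already provides for extraction of the medical history.
2. Beside the asymmetry index, compare the operated limb's 1-year values (strength, kinematics, kinetics) between arms, adjusted for the preoperative value. State beforehand which direction counts as better for each parameter.
3. Conclude better recovery under Hypothesis 2 only if the operated-limb results agree with the index.
4. Repeat the asymmetry analysis in patients whose opposite knee was unaffected at baseline. Define this subset by baseline status only, so that it does not depend on events after randomization. Report new opposite-knee surgery by arm instead of excluding for it.

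The cost is a few case-report items, a little more analysis, and somewhat fewer patients in the restricted asymmetry analysis. Strength is already measured on both legs, so no new measurement is needed, and neither eligibility nor treatment changes.

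### As written, the ratio asymmetry index also covers gracilis onset and offset times, where it measures position in the gait cycle rather than the gap between the limbs

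*Protocol article*

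**What the plan says.** Four statements in the protocol article matter here.

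- Biomechanical assessment, ratio index: "For all muscle strength, gait spatio-temporal, and muscle activity parameters, the asymmetry index (AI) will be calculated" as |1 − lower/higher|, with the limbs ordered by value and not by operated side.
- Same section, difference index: "For all kinematic and kinetic parameters (measured in degrees respective Nm/kg), the asymmetry index will be defined as" the absolute difference between the higher and the lower limb. This form is also unsigned.
- Same section, timing: "Timing of the gracilis muscle will be assessed as on- and offset relative to the gait cycle". The section's opening list of outcomes includes "isokinetic muscle strength, gait asymmetry, single-legged drop landing, and timing of muscle activity", so the protocol itself describes timing as a feature of muscle activity.
- Specific aims: Hypothesis 2 says that dynamic patients "will have less asymmetry in muscle strength and lower extremity gait kinematics and kinetics". Hypothesis 3 describes the gracilis as having "normal activity from pre-swing throughout the entire swing phase to the beginning of the loading response", and adds: "We anticipate that muscle activity will shift more toward the loading response and the whole stance phase at knee angles < 30° of flexion".

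The Statistical analysis section compares the arms by differences in means. The article states no exception for timing, no circular handling and no signed index.

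**The concern.** A ratio of two limb values is meaningful only if zero means none of the quantity. That holds for torque and EMG amplitude. It does not hold for a time point expressed as a share of the gait cycle: the scale wraps round, and its zero is a convention. Close to that zero, a small denominator inflates the index. Across it, two nearly simultaneous events are scored as almost maximally asymmetric.

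The protocol's own description puts gracilis offset, and the shift expected after surgery, in that region. Differences between arms in the timing index could therefore arise from where the events lie, even if the limbs are equally well matched in both arms.

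A lesser issue concerns the remaining parameters. Because the limbs are ordered by value, the index cannot separate a deficit of the operated limb from a surplus. It is also positive when the limbs are truly equal but measured with noise.

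**Working it through.** **Inputs.** The index AI = |1 − lower/higher| and the gait-cycle time scale come from Biomechanical assessment; the location of gracilis activity comes from Hypothesis 3. Assumptions, because the article gives no figures: timing in percent of cycle, initial contact = 0, and all spreads and limb ratios below. Simulations use 27 patients per arm, the evaluable number in the Sample size calculation, and a two-sample t-test.

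**1. Timing, direct evaluation.** The true gap is min(|a − b|, 100 − |a − b|).

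| Limb times (% of cycle) | True gap | AI |
|---|---|---|
| 2 vs 5 | 3 | 1 − 2/5 = 0.60 |
| 62 vs 65 | 3 | 1 − 62/65 = 0.05 |
| 50 vs 60 | 10 | 1 − 50/60 = 0.17 |
| 98 vs 3 | 5 | 1 − 3/98 = 0.97 |

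The first two rows also show that the zero is arbitrary: they are the same pair of events with the origin moved by 60 points. A 10-point gap in mid-cycle scores far lower than a 3-point gap near the boundary.

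**2. Timing with no true limb difference.** Each limb varies independently with an assumed SD of 3 points around the same mean. The expected gap is 3 × √2 × √(2/π) = 3.4 points wherever the event lies. The mean AI is not constant:

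- event at 60%: 0.05
- at 30%: 0.10
- at 10%: 0.28
- at 5%: 0.48
- at 2%: 0.66

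Two groups with identical limb agreement, one centred at 10% and the other at 5%, would differ in mean AI by 0.48 − 0.28 = 0.20.

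**3. Other parameters: direction.** An operated limb at 80% of the other scores 1 − 80/100 = 0.20. At 125% it scores 1 − 100/125 = 0.20.

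**4. Other parameters: noise floor.** With equal true limb values and an assumed log-ratio SD of 0.10, the mean AI is 0.075.

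**5. Other parameters: power.** Signed log ratio against unsigned AI, with assumed operated/contralateral ratios in the two arms:

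| Ratios | SD of log ratio | Signed | AI |
|---|---|---|---|
| 0.90 vs 1.00 | 0.08 | >99% | 83% |
| 0.90 vs 1.00 | 0.12 | 89% | 32% |
| 0.90 vs 1.00 | 0.20 | 48% | 9% |
| 0.85 vs 0.95 | 0.12 | 92% | 75% |
| 0.80 vs 0.90 | 0.12 | 94% | 91% |
| 0.75 vs 0.85 | 0.12 | 96% | 96% |
| 1.00 vs 1.00 | 0.20 vs 0.08 | 5% | 98% |

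The loss is large when one arm sits at symmetry and the spread is wide. It nearly vanishes when both arms keep a clear deficit. In the last row the arms differ only in spread, and there the signed comparison is the one that fails.

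**The case against.** **On timing.** The phrase about muscle activity could be meant only for the EMG amplitude defined in the same paragraph, for which a ratio is valid. That may be the intention, but the text says all such parameters, comes directly after the definition of gracilis onset and offset, and makes no exception. It is also fair that the index is a cited, published one. That supports its use on quantities with a true zero, not on cyclic times.

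**On reach.** A reader might infer that the timing defect undermines Hypotheses 2 and 3. The article does not support this. Hypothesis 2 names strength, kinematics and kinetics, not timing. Hypothesis 3 can be examined on onset and offset as such, which the protocol also records. This objection stands and confines the defect to the asymmetry index applied to timing.

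**On the unsigned index.** A reader might also infer that dropping the sign makes the index wrong for Hypothesis 2, or that it generally wastes most of the power. Neither holds. The hypothesis is "less asymmetry in muscle strength and lower extremity gait kinematics and kinetics than patients with static MPFL reconstruction", a statement about amount with no limb direction, and an unsigned index measures amount. With ratios of 0.95 and 1.05 (SD 0.12) the signed test rejects in about 85% of trials and the AI in 5%. But the mean AI is 0.096 in both arms, so neither arm is less asymmetric and 5% is the correct rate. Replacing the AI by a signed primary measure would be a trade-off, as the last row of the power table shows.

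**Conclusion.** The rule as written is wrong for gracilis onset and offset. Near the cycle boundary the index can differ more than tenfold for the same gap (0.60 against 0.05 for 3 points) and can approach 1 for limbs 5 points apart. This rests on two readings: that timing counts as a muscle activity parameter, which the article's own wording supports, and that initial contact is the zero. Another zero would move the problem to another part of the cycle without removing it. The mean values in step 2 also rest on the assumed SD of 3 points; the direct evaluations in step 1 do not.

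For the other parameters the unsigned index is an acceptable match to Hypothesis 2. Its loss of direction and its noise floor are reasons to report more beside it, not to replace it. The power cost depends on SDs that the article does not give.

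The point should be corrected, but its reach is limited to secondary biomechanical outcomes. The Kujala comparison and the target of 60 patients are untouched.

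**What to change.** 1. Exclude gracilis onset and offset from the ratio index. Use the operated-minus-contralateral difference in percent of gait cycle, wrapped to ±50, and its absolute value where the amount of asymmetry is the question. State which event defines zero.
2. For strength, spatio-temporal, EMG amplitude, kinematic and kinetic parameters, keep the unsigned index as the measure for Hypothesis 2. Report the signed value beside it: log(operated/contralateral) for the ratio-type parameters, and operated minus contralateral for kinematics and kinetics. Readers can then tell a deficit from a surplus and see when an arm is near the noise floor.

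Both steps are recalculations from bilateral recordings already planned, with no added measurement or patient. The cost is slightly less comparability with papers that apply the cited index to timing.
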